### Upper extremity functioning

Physical functioning will be assessed on three different levels, in accordance with the International Classification of Functioning [33]. Patients' performance on impairment, activity and participation levels will be assessed.

1. *Upper extremity functioning at the impairment level *will be assessed using two instruments, described below.

*1.1 *The arm section of the Fugl-Meyer Test (FMT) contains three different domains: (a) motor function (24 items; scores range from 0 to 66), (b) sensation (6 items; scores from 0 to 12) and (c) passive joint motion/joint pain (12 items, scores from 0 to 48)[34]. Each item is scored on a 3-point ordinal scale. The Fugl-Meyer Assessment of the Upper Extremity (FMA-UE) is the most widely used clinical assessment of post-stroke upper extremity impairment [35] and showed a very high inter-rater and test-retest reliability (ICC > 0.95) [35,36].

*1.2 *To score spasticity level, the Tardieu Scale will be used. The affected limb is passively moved through range at two velocities – i.e., as fast and as slow as possible (VI). At both velocities, the quality of the muscle reaction to stretch is assessed for each muscle group, and the angle at which the muscle reaction occurred is measured with a hand-held goniometer after the cessation of movement. Spasticity will be scored from 0–4 during the fast stretching velocity. In patients with severe brain injury and impaired consciousness, the Modified Tardieu Scale provides higher test-retest and inter-rater reliability than the Modified Ashworth Scale and may therefore provide a more valid spasticity scale for adults [37].

*2. Upper extremity functioning at the activity level *will measured using the following three instruments.

*2.1 *The Wolf Motor Function Test (WMFT) test contains 15 timed and 2 strength tasks (lifting of weighted limb and grip strength), ranging from simple to complex and administered sequentially to each upper extremity while controlling for patient positioning. Trained observers rate quality of movement using a 6-point functional ability scale (0 = no attempt; 5 = normal movement). Strength and performance time will be recorded by the test administrators. The psychometric properties of the WMFT appear solid [4,38-40].

*2.2 *The Frenchay Arm Test (FAT) will be used to assess the degree to which the patient is able to actually perform arm hand functions and tasks. It includes an evaluation of performance on five different tasks, and has shown good reliability and validity in stroke patients [26].

*2.3 A*ccelerometery (ACC) will be used to assess upper extremity use in a daily life situation. Patients will wear a 'watch' with an accelerometer inside (Actiwatch [41]) on both wrists for three days, during waking hours. This Actiwatch includes two uniaxial piezoresistive accelerometers used to record the amount of movement based on accelerations. Within both watches the rectified and integrated acceleration from two directions over one minute are registrated. The number of occasions on which this signal exceeds a predefined threshold is then calculated. The outcome is expressed in counts per minute, based on wrist accelerations. Data collection will continue uninterrupted for three days, with output stored in a data memory chip within the accelerometer and read out by a computer after this time.

The Actiwatch has shown good validity for assessing daily life activities [41]. In stroke, several studies have shown that accelerometry provides an objective, real-world index of arm activity with strong psychometric properties [42-45]. In the present study, an activity index will be calculated as a ratio between the activity of the impaired arm movement and that of the unimpaired arm movement. Uswatte et al. found that in stroke patients, a ratio score controls adequately for variations in overall levels of physical activity, and is a reliable and valid real-world measure of upper extremity treatment outcome [39].

*3. Functional performance on the level of participation in society and perceived quality of life *will be measured using three methods.

*3.1 *The Impact on Participation and Autonomy (IPA) questionnaire. This 39-item questionnaire focuses on two aspects of participation: the perceived participation level in different domains, and the problems encountered [46,47].

3.2 The Stroke-Specific Quality of Life (SS-Qol) scale. This includes an overall evaluation of the patient's quality of life compared with their pre-stroke state. Twelve domains are included: personality, energy, language, mobility, vision, upper extremity function, thinking, mood, work/productivity, self care and family and social roles [48].

*3.3 *The EuroQol 6D (EQ-6D). This is a generic measure scoring quality of life using six domains: mobility, self-care, usual activities, pain/discomfort, anxiety/depression and cognition. Each domain consists of three answer possibilities. Participants are also to rate their current health state on a visual analogue scale from 0 to 100 [49].

In brief, primary outcome measures for the evaluation of upper extremity functioning focus on the activity level (WMFT, FAT, ACC), whereas secondary outcome measures focus on both the impairment (FMT) and participation level (IPA, SS-Qol).

### Process evaluation

After completing the intervention, participants will be asked to evaluate it by way of a questionnaire. In addition, treatment compliance in both groups will be monitored using diaries recording the daily amount of time patients spend on mental practice training (intervention group) and NDT-based upper extremity training (control group). Compliance can be an important issue in studying patients in the sub-acute stroke phase [10]: poor compliance can negate interpretation of the outcome as reflecting the therapy's effectiveness. Through diary use, however, compliance is rendered objective. The intervention process will also be evaluated based on information provided by occupational therapists, who will record the following items: the number of consultations, the provision of information per consultation, the kind of problems presented, completion of the intervention according to protocol and reasons for non-compliance (where applicable).

### Determination of costs

Both direct non-medical and indirect costs will be measured using a cost questionnaire administered to the participants or their proxies at the time of the T0-T4 assessments [50]. An additional cost questionnaire will be sent to the patient at 9 months. With society's perspective for the economic evaluation, all relevant rehabilitation costs will be determined using a micro-costing approach. This means that the unit size of the resource used will be multiplied by the respective unit cost across patients to estimate the aggregate cost for society [51]. Healthcare resources used in administering the intervention as well as direct medical costs would include contact with professionals (e.g., physicians, therapists and rehabilitation nurses or formal caregivers), equipment and materials (e.g., orthoses), assessment tools, and medications (particularly anti-spasmodics and muscle relaxants). Along with allocated overhead costs, these measures will determined through the institutions' administrative records.

Direct non-medical costs include patient times, transportation and out-of-pocket expenses not covered by insurance. Indirect costs would cover productivity losses and informal care by the family or significant others. In line with recommendations in the Dutch manual for costing in economic healthcare evaluations, standardized costs will be used [52]. Medications will be valued based on the Daily Defined Dosage (DDD) price list from the Dutch Pharmacotherapeutic Compass [53]. Productivity losses will be valued using the friction cost method, which bases calculations on the 'friction period,' or the time needed to replace a sick employee. Informal care (considered unpaid work) would be valued using shadow prices.

### Statistical analysis

#### Effect evaluation

The number of dropouts (patients who prematurely end their participation) and follow-up losses in both training groups will be reported based on descriptive data. Baseline characteristics of compliant and non-compliant participants will be compared. Before examining the intervention's effectiveness, possible differences between the two groups will be determined by comparing baseline characteristics using independent sample T-tests (normal distribution) or Mann Whitney U-tests (non-normal distribution) in the event of continuous variables. In cases of dichotomous variables, a chi-square test will be used.

The effects of mental practice-based therapy on arm function outcome will be evaluated using MAN(C)OVA and GEE (generalized estimated equations) analyses. Deviations from the therapy protocols will be analyzed according to the 'intention-to-treat' principle. If either T2 or T4 data are missing, the 'last-observation-carried-forward' principle will be used. Losses of T0 and/or T1 data will lead to exclusion, and an additional participant will be entered into the project. Subgroup analysis will be performed for potential effect modifiers.

To assess whether protocol deviations or care provided outside the intervention have caused bias, the results of the intention-to-treat analysis will be compared to the on-treatment analysis.

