## Background

The incidence of stroke in the Netherlands was 2.2/1000 in 2000 [1]. Over 50% of patients with upper limb paresis resulting from stroke face long-term impaired arm function and a ensuing disability in daily life [2]. Although early rehabilitation treatment in the first phase of stroke is currently advised in clinical guidelines, little evidence is available on such treatment for improving arm/hand function in the same period [3]. Recently, constrained induced movement therapy (CIMT), in which the affected arm must be used due to immobilizing the other, appears to have had a positive effect on arm/hand function in sub-acute stroke patients [4]. However, even long after the stroke only small arm function improvements are reported in a select minority of patients, which stands in contrast to the far better recovery of leg function.

Some studies have shown task-oriented treatment to positively affect arm function recovery in stroke patients [5]. More recently, 'movement imagery' has emerged, targeting the cognitive processes associated with enhanced motor performance and specific skilled movements in healthy persons. Regularly applying this technique in training and competition is called 'mental practice'. Sports psychology research has shown that mental practice can optimize athletes' execution of movement and acquisition of new, skilled behaviors [6,7]. Moreover, combining mental practice training principles with active movement training appears more beneficial than mental practice training alone [6].

In neuroscience, interest in movement imagery has grown in line with improvements in brain mapping techniques. Results from brain imaging experiments suggest that executed and imagined movements share a common neural substrate [8-10]. This has led to the hypothesis that mental practice may contribute to the activation of neural loops and movement patterns for which the brain has a kind of motor print [11]. Mental practice might be used alongside physical rehabilitation in patients with neurological disorders and will probably be most effective in the early recovery stage during which the reorganization of brain patterns is most prominent [10].

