The possible benefits of movement imagery on motor performance in acute and chronic stroke patients have been investigated in several studies. Page et al., in a small feasibility study using movement imagery in stroke patients, found a marked improvement in their arm function compared to that of the control group [12]. Similar effects in the training of neglect and motor skills have been reported by Smania et al. and Yoo et al. [13,14]. It seems, then, that although the brain is damaged by stroke, the ability to train using mental practice is retained.

The effects of mental practice on small chronic stroke groups have been reported in several studies [14-22] using different mental practice techniques and intensities. In 2006, Braun et al. presented a systematic review focusing on effectiveness of mental practice training in improving upper extremity functioning, but drew no definite conclusions except that further research using clear definitions of mental practice content and standardized outcome measurements are needed [21]. In 2007, based on a randomized controlled trial for chronic stroke patients, Page et al. confirmed the short-term effectiveness of mental practice in improving upper extremity function [23].

Only one article has reported on the long-term effect of mental practice in stroke patients. This was based on an evaluation conducted just one month after training; the conclusions were positive [22]. The effectiveness of mental practice in stroke, however, is likely influenced by factors such as the ability to perform motor imagery, cognitive functioning, gender, handedness, dysphasia, precise lesion location and time elapsed since the stroke [10,24]. Whether these factors are indeed predictive of therapy outcome and whether mental practice is also effective over the long term in sub-acute stroke patients is currently unknown.

Based on the latest body of evidence, it is hypothesized that mental practice applied in a training regime involving arm function tasks will lead to a significant and long-lasting improvement in stroke patients' arm function. Furthermore, since rehabilitation depends upon the learning of new behaviors (this is associated with brain plasticity), the treatment should include much repetition [2], start early after the stroke [2], be personally rewarding to the patients and provide as much experience as possible of various activities.

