### Data collection

Measurements will be taken upon entry to the study (T0 = baseline) and 6 weeks (T1 = post treatment); 6 months (T2 = short-term follow-up); 9 months (T3 additional cost questionnaire) and 12 months (T4 = long term follow up) after T0. They will be performed by a rater blinded for therapy modality, and administered wherever the patient is at the time. A blinding check will be performed after each of the four measurement sessions.

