### Outcome measures

Outcome measures and assessment moments are presented in table 2.

**Table 2 T2:** Outcome domains and assessment instruments and moments

**Domain**	**Assessment instrument**	**Abbr.**	**T0**	**T1**	**T2**	**T3**	**T4**
Medical information	- Brain lesion		X				
	- Type of stroke		X				
	- Co-morbidity		X				
Basic level of functioning	- Barthel score	BI	X		X		X
	- Frenchay Activity Index	FAI	X*	X	X		X
Cognitive functioning	- Cognitive Log	Cog-log	X				
	- Vividness of Movement Imagery Q.	VMIQ	X				
	- Credibility/Expectancy Q.	CEQ	X				
UEF level of impairment	- Brunnstrom-Fugl-Meyer test	FM	X	X	X		X
	- Strength: part of WMFT	WMFT _str_	X	X	X		X
	- Spasticity: Tardieu scale	MTS	X	X	X		X
UEF level of activity	- Wolf Motor Function Test	WMFT	X	X	X		X
	- Frenchay Arm Test	FAT	X	X	X		X
	- Accelerometry	ACC	X	X	X		X
UEF level of participation	- Impact on Participation and Autonomy questionnaire	IPA					X
	- Stroke-Specific Quality of Life	SS-Qol					X
	- EuroQol	EO-6D		X	X		X
Cost	- Cost questionnaire	CQ	X	X	X	X	X
Process evaluation	- Diary		X				

T0 = baseline

UEF = upper extremity functioning

T1 = 10 weeks after T0

T2 = 6 months after T0

T3 = 9 months after T0

T4 = 12 months after T0

* The FAI on T0 retrospectively assesses the pre-morbid activity level

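### Last observation carried forward at 6 and 12 months mixes earlier treatment contrasts into the test of a lasting effect; the bias is modest at the planned loss but its direction cannot be known in advance

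*Protocol article*

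**What the plan says.** Under Effect evaluation the Protocol article sets two rules for missing data. For the follow-up visits: "If either T2 or T4 data are missing, the 'last-observation-carried-forward' principle will be used". For the earlier visits: "Losses of T0 and/or T1 data will lead to exclusion, and an additional participant will be entered into the project". Every analysed patient therefore has a T1 score available to carry forward.

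Effects on arm function "will be evaluated using MAN(C)OVA and GEE (generalized estimated equations) analyses". No other missing-data method is named, and no sensitivity analysis to this one. The one comparison of analyses that is planned, in which "the results of the intention-to-treat analysis will be compared to the on-treatment analysis", is aimed at protocol deviations and care outside the intervention, not at missing data.

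Under Data collection, the visits after baseline are at "6 weeks (T1 = post treatment); 6 months (T2 = short-term follow-up); 9 months (T3 additional cost questionnaire) and 12 months (T4 = long term follow up) after" study entry. Table 2 shows only the cost questionnaire at T3, so the last arm-function assessment before T4 is T2.

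The Background hypothesises that the training "will lead to a significant and long-lasting improvement in stroke patients' arm function", and says that long-term effectiveness in sub-acute patients is currently unknown.

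**The concern.** Carrying a score forward asserts that the patient did not change after the last visit. Patients enter 2–6 weeks after stroke (Table 1). The Background expects mental practice to work best in "the early recovery stage during which the reorganization of brain patterns is most prominent". A flat course from the end of a six-week treatment to 6 months, or from 6 to 12 months, is therefore a strong assumption in this population.

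The durability question makes it matter more. The 6- and 12-month comparisons are there to show whether an effect seen at the end of treatment lasts. For each patient with a filled-in value, the rule supplies the earlier answer as if it were the later one. A fading effect then looks more durable than it is, and a late effect looks smaller. If the arms lose different proportions of patients while both are still improving, a difference appears or disappears for reasons unrelated to treatment.

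**Working it through.** **Inputs.** From Study population: mean WMFT functional ability score 3.91, SD 1.11, relevant difference 10%, follow-up loss about 10%, 80 per arm. The target difference is 0.10 × 3.91 = 0.391 points. The plan gives no figure for the effect of carrying forward, so there is none to reproduce. It also gives no change after T1, loss by arm or within-patient correlation; those values below are assumptions.

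**Step 1: which score is carried.** T2 missing: T1 is used. T4 missing with T2 present: T2 is used. Both missing: T1 is used for both. If a fraction a misses only T4 and a fraction b misses both, equally in the two arms and unrelated to outcome, the expected T4 contrast is (1 − a − b) × d(T4) + a × d(T2) + b × d(T1), where d is the true contrast at each visit.

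**Step 2: equal loss.** Write m for total loss and d(last) for the contrast at the last observed visit:

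expected contrast = (1 − m) × d(T4) + m × d(last), so bias = m × (d(last) − d(T4)).

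- m = 0.10, contrast of 0.391 that vanishes: 0.10 × 0.391 = +0.039, or 10% of the target.
- m = 0.10, contrast that emerges late (0, then 0.391): −0.039.
- m = 0.10, constant contrast: 0.
- m = 0.20 or 0.30, contrast that vanishes: +0.078 or +0.117.

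**Step 3: unequal loss.** Assume no treatment effect at any visit and a mean gain g after the last visit in both arms. Freezing a patient then removes g from that patient's score:

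bias = (loss in control − loss in intervention) × g.

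With 5% lost in intervention and 15% in control:

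- g = 0.25: 0.10 × 0.25 = 0.025 (6% of 0.391)
- g = 0.5: 0.10 × 0.5 = 0.05 (13%)
- g = 1.0: 0.10 × 1.0 = 0.10 (26%)

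If the losses are swapped, the sizes stay the same and the sign reverses, against the intervention.

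**Step 4: error rates.** The general form is (1 − mI) × d(T4) + mI × d(last) + (mC − mI) × g, with mI and mC the losses in intervention and control. It was checked by simulation: 80 per arm, SD 1.11, assumed correlation 0.8, g = 0.5, loss at random, two-sided t-test at T4, 6,000 runs.

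| Loss, intervention/control | d(last) | d(T4) | Formula | Simulated mean | Rejections, carried forward | Rejections, observed data |
|---|---|---|---|---|---|---|
| 10%/10% | 0.391 | 0 | 0.039 | 0.040 | 5.5% | 4.7% |
| 20%/20% | 0.391 | 0 | 0.078 | 0.079 | 7.7% | 5.1% |
| 5%/15% | 0 | 0 | 0.050 | 0.049 | 5.7% | 4.8% |
| 5%/15% | 0.391 | 0 | 0.070 | 0.068 | 7.2% | 4.9% |
| 0%/20% | 0.391 | 0 | 0.100 | 0.100 | 8.4% | 4.5% |
| 15%/5% | 0.391 | 0.391 | 0.341 | 0.336 | 46% | 54% |

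In the first five rows rejections are false positives at T4. In the last row they are power. Power there is well below the planned 85% even on observed data because 160 patients give only about 61% for 0.391 with SD 1.11; that is a separate sample-size matter. The observed-data column is unbiased because loss was simulated as unrelated to outcome.

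**Step 5: standard errors.** With no treatment effect, equal loss and all losses filled from T1, the empirical and model standard errors were 0.179 and 0.179 at 10% loss and 0.183 and 0.182 at 20%. Type I error was 5.1% in both cases. The inflation in Step 4 comes from a biased contrast, not from understated standard errors.

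**The case against.** The best defence is that the damage is small and bounded under the plan's own figures. The end-of-treatment comparison is untouched. At 10% equal loss the T4 bias cannot exceed about 0.039 points for contrasts between 0 and 0.391, and it is zero for a stable effect. Losses are to be reported by group, so an imbalance would be visible. Carrying forward also has a practical purpose: MAN(C)OVA in its standard form needs complete rows. All of this stands and limits the weight of the point. It does not supply a reason to assume no change when a model on the observed data is available.

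Five stronger readings are tempting, and the document does not support them.

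- *That T1 is routinely carried to 12 months.* It is carried that far only when T2 is also missing.
- *That the rule favours the intervention.* The direction depends on whether the effect fades or grows and on which arm loses more patients.
- *That most patients must change a lot after T1.* The remark on early recovery concerns when mental practice may work best. The Background also says that, long after stroke, only small improvements are reported, in a minority of patients. No figure in the document supports large later gains.
- *That standard errors are necessarily too small.* Step 5 does not show this.
- *That the rule breaks down for scales measured once.* Table 2 lists the "Impact on Participation and Autonomy questionnaire" and SS-Qol only at T4, so they have nothing to carry forward. But the rule sits with the arm-function analysis, and the article does not say it covers these scales. Their handling, like that of deaths, may be left to the full plan.

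**Conclusion.** The point holds in moderate form. The rule is stated, has no missing-data sensitivity analysis beside it, and conflicts with the purpose of the 6- and 12-month comparisons. At the planned loss, equal between arms, it shifts the T4 contrast by up to about a tenth of the target difference and leaves type I error near 5.5%. With higher or unequal loss the shift was 0.05 to 0.10 points in the simulated scenarios with no true T4 effect, with type I error of 5.7% to 8.4%. With more loss in the intervention arm, it hides part of a real lasting effect.

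The equal-loss result rests on the plan's 10% and on contrasts between 0 and 0.391. The unequal-loss results rest on assumed loss splits and gains. For patients missing only T4, the relevant gain is that from T2 to T4, which may be smaller than the gain from T1. None of these scenarios reverses an effect of 0.391; the risk is a distorted durability conclusion.

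T1 is given as 6 weeks under Data collection and 10 weeks under Table 2. These statements must be reconciled, but the result here does not depend on which applies.

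**What to change.** Replace carrying forward as the main analysis of the follow-up arm-function outcomes. Use a likelihood-based repeated-measures model on the observed T1, T2 and T4 scores, with the baseline value, group × visit and the stratification factors (MRC 1 versus 2–3, and hospital). Report the T2 and T4 contrasts from it. The model is valid under missing at random and needs no filled-in values.

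Add a multiple-imputation sensitivity analysis in which imputed scores are shifted over a stated range, to show how far departures from missing at random would change the T4 result.

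If GEE is kept, say how loss is handled. Unweighted GEE on available visits needs the stricter assumption that loss is unrelated to outcome given the covariates. Dropping the filled-in values and relying on it alone is therefore only a partial remedy.

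The cost is revised wording and a little more analysis in standard software. No new data are needed. The change should be made before outcome data are seen by group.

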### Recruitment and randomization

Patients admitted to the participating institutions will be evaluated on the basis of the inclusion criteria by a consultant in rehabilitation medicine involved in treatment within three days of admission to a stroke service. Time lapsed since the stroke occurred should preferably be less than two weeks. If the patient is still unconscious or incapacitated at this time, inclusion may take place as appropriate within the ensuing four weeks. Standard informed consent procedures will be used. Participants will then be randomly allocated to either the intervention or control group, with the computerized (block) randomization scheme including pre-stratification according to two variables: MRC scale of the elbow flexor (dichotomized in score 1 or scores 2–3); and participating hospital. Two sets of opaque, numbered envelopes will be prepared for each site (one each for MRC score 1 and MRC scores 2–3) containing cards indicating the allocated group. When a new patient is registered, a card will be extracted and the relevant occupational therapist informed of the group allocation.

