### Intervention and control group

In accordance with Dutch stroke rehabilitation guidelines, the intervention group patients will receive their regular therapy [3] and additional mental practice-based arm function training. This training will be supervised by the rehabilitation team occupational therapist. After baseline measurements are performed, patients will be familiarized with the mental practice-based therapy during the first session. The patient is educated as to basic imagery principles and the importance of regular imagery training in increasing therapy success. During the first week, the patient will be taught how to use the mental practice techniques to improve arm function by the occupational therapist. A training task tailored to the functional level of the individual patients will be selected by the occupational therapist.

Five different mental practice training tasks derived from the Frenchay Activities Index [26] are available, with gradually increasing difficulty. For all tasks, a training DVD will guide the patient. Each DVD is programmed in three steps starting with a relaxation task to focus attention. Performance of all activities is shown from a 1^st ^person perspective (an 'over-the-shoulder' view). In the first step, correct task performance is shown on screen combined with a verbal explanation. Five repetitions are given. In the second step, task performance is repeated on screen but without verbal explanation; patients are asked to mentally practice the movement. If they are able to actually perform (part of) the task, they may do so concurrently with the imagination of the movement. Again, five repetitions are given. In the third step, no guidance during task performance is given except a visual and verbal cue indicating the end of the task performance over five repetitions. Patients already familiar with this task can immediately start on step two.

DVDs are available for every task for right- and left-handers. Patients must practice at least three times a day for ten minutes each session. During the intervention period, functional arm/hand progress will be evaluated by the occupational therapist every two weeks. If functional level improves, a new task will be chosen and the DVD changed. The total intervention lasts six weeks.

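### Randomised patients with missing T1 data are excluded and replaced, so the analysis labelled intention-to-treat omits some randomised patients and can be biased

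*Protocol article*

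**What the plan says.** The protocol article, Effect evaluation, has two rules for missing data. For the later visits the patient is kept: "If either T2 or T4 data are missing, the 'last-observation-carried-forward' principle will be used". For the first two visits the patient is removed: "Losses of T0 and/or T1 data will lead to exclusion, and an additional participant will be entered into the project".

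The same section invokes intention-to-treat twice. First: "Deviations from the therapy protocols will be analyzed according to the 'intention-to-treat' principle". Then, as a check on bias from protocol deviations or outside care, "the results of the intention-to-treat analysis will be compared to the on-treatment analysis". The effects on arm function "will be evaluated using MAN(C)OVA and GEE (generalized estimated equations) analyses".

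On timing, Data collection says: "Measurements will be taken upon entry to the study (T0 = baseline) and 6 weeks (T1 = post treatment". (The footnote to Table 2 puts T1 at 10 weeks; on either timing T1 falls after allocation.) Recruitment and randomization says, after the consent step: "Participants will then be randomly allocated to either the intervention or control group". It does not place T0 before or after that step. Intervention and control group puts T0 before therapy starts: "After baseline measurements are performed, patients will be familiarized with the mental practice-based therapy during the first session".

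**The concern.** An intention-to-treat comparison rests on analysing the groups that randomisation formed. Whether a patient provides T1 data is decided after allocation. Tolerance of the training, motivation, recovery, deterioration or death could all affect it. Selecting on it means that the two analysed groups are no longer guaranteed to be comparable.

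Replacement does not repair this. If the new participant takes the next envelope, the depleted arm need not be the one refilled. If the participant is placed in the depleted arm on purpose, that allocation is not random. Either way the patient who was lost remains out of the comparison.

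Two further consequences follow. A patient who misses T1 but attends T2 and T4 loses all of those data, while a patient who misses T2 or T4 is retained. And patients lost before T1 are absent from both the intention-to-treat and the on-treatment set, so comparing the two cannot reveal bias from their removal.

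**Working it through.** **Step 1: what is fixed by the text.**

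| Visit missing | Rule | After randomisation? |
|---|---|---|
| T0 | exclude and replace | not stated |
| T1 | exclude and replace | always |
| T2 or T4 | carry last observation forward | always, but patient kept |

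The conflict with the intention-to-treat label is certain for T1. For T0 it exists only if T0 is taken after allocation.

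**Step 2: the target.** Study population gives a mean functional ability score of 3.91, an SD of 1.11 and a relevant difference of 10%. So 0.10 × 3.91 = 0.391 points. The article gives no figure for T1 loss by arm and none for bias, so there is nothing of its own to reproduce beyond this.

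**Step 3: the bias formula.** Let p be the share of an arm lost at T1, and k the retained mean minus the lost patients' mean. The all-randomised mean is then the retained mean minus p × k, so analysing only the retained overstates that arm by p × k. With the same k in both arms:

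bias = (p_exp − p_ctl) × k

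**Step 4: illustration.** All p and k are assumptions.

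| Loss, experimental vs control | k (points) | Bias (points) | Share of 0.391 |
|---|---|---|---|
| 10% vs 10% | any, same in both arms | 0 | 0% |
| 7% vs 5% | 0.5 to 1.0 | 0.01 to 0.02 | 3% to 5% |
| 10% vs 3% | 0.5, 1.0, 1.5 | 0.035, 0.07, 0.105 | 9%, 18%, 27% |
| 15% vs 5% | 0.5, 1.0, 1.5 | 0.05, 0.10, 0.15 | 13%, 26%, 38% |
| 5% vs 15% | 0.5, 1.0, 1.5 | −0.05, −0.10, −0.15 | −13%, −26%, −38% |

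The sign also reverses if the lost patients are the better performers (k negative). Equal loss alone is not enough for zero bias. If k differs by arm, the bias is p_exp × k_exp − p_ctl × k_ctl. For example, 10% loss in each arm with k of 1.0 and 0.5 gives 0.10 − 0.05 = 0.05 points, or 13% of the target.

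**Step 5: effect on the test.** Take the article's 145 analysed patients as given (72.5 per arm) and no true effect. The standard error is 1.11 × √(2/72.5) = 0.184. Expressing k as 0.5 to 1.0 SD (0.555 to 1.11 points):

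- 10% vs 5% loss: bias 0.03 to 0.06 points; two-sided type I error 0.053 to 0.060.
- 15% vs 5% loss: bias 0.06 to 0.11 points; two-sided type I error 0.060 to 0.092.

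**The case against.** The strongest defence is that the harm is hypothetical. Therapist contact is planned to be equal, both arms have the same practice prescription, and assessments are done wherever the patient is, so stopping therapy need not mean missing T1. The article expects only about 10% loss over the whole follow-up, and 15% versus 5% averages 10%, so that scenario uses the entire allowance by T1. With a small imbalance the bias is a few per cent of the target. This stands as a limit on size. It does not reconcile the exclusion rule with the intention-to-treat label.

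It can also be said that the first intention-to-treat sentence covers only deviations from therapy. Read alone, it does. The later sentence, however, names the main analysis as the intention-to-treat analysis.

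Four stronger readings are tempting, and the article does not support them:

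- A reader might infer that the comparison is biased for certain. It is not; like-for-like loss gives zero.
- A reader might call the analysed set treatment completers. It is not; patients who stop or under-practise but are assessed at T1 stay in, and those lost after T1 are kept.
- A reader might conclude that the comparison with the on-treatment analysis is worthless. It still contrasts non-compliers who were seen at T1, so it is weakened, not emptied.
- A reader might extend the rule to every outcome. It stands under Effect evaluation, which concerns arm function, and nothing applies it to the economic evaluation.

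Finally, a model that assumes data missing at random would not in general remove outcome-dependent bias. That is correct, and the fix allows for it.

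**Conclusion.** The point holds for T1. A stated rule removes randomised patients because of a post-randomisation event, while the plan labels the result intention-to-treat. Dropouts and losses are to be reported descriptively, which discloses the problem but does not correct it, and the article describes no analysis that brings the excluded patients back. For T0 the point is conditional on the order of baseline measurement and allocation, which the article leaves open.

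The case for changing the rule rests on that contradiction and not on any percentage. The 13% to 38% range depends wholly on an assumed 15% versus 5% loss and an assumed gap of 0.5 to 1.5 points. It shows what is possible, in either direction, not what is likely.

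**What to change.** 1. Delete the exclusion-and-replacement sentence.
2. State that T0 is completed before the envelope is drawn, so that a missing baseline cannot arise after allocation.
3. Analyse every randomised patient in the allocated group, and continue to collect T2 and T4 from patients who miss T1.
4. Handle missing T1 with a repeated-measures model that keeps incomplete series: a mixed model, or the planned GEE with multiple imputation.
5. Add a sensitivity analysis for data missing not at random, for example by shifting the imputed values by arm.
6. Report T1 losses and their reasons by arm. Present the set with both T0 and T1 data only as a sensitivity analysis.

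The cost is modest but more than one sentence. The carry-forward rule and the MAN(C)OVA wording must be aligned with the new approach, and the imputation and sensitivity analyses are extra work. Slightly fewer patients may have complete T1 data. The planned 160 already allows for about 10% loss (160 × 0.90 = 144, against the stated 145), so replacement is not needed to absorb loss of that order.
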